## Abstract

**Background:**

Chronic widespread pain (CWP), including fibromyalgia (FM), affects one in every ten adults and is one of the leading causes of sick leave and emotional distress. Due to an unclear etiology and a complex pathophysiology, FM is a condition with few, if any, effective and safe treatments. However, current research within the field of vagal nerve innervation suggests psychophysiological and electrical means by which FM may be treated. This study will investigate the efficacy of two different noninvasive vagal nerve stimulation techniques for the treatment of FM.

**Methods:**

The study will use a randomized, single-blind, sham-controlled design to investigate the treatment efficacy of motivational nondirective resonance breathing (MNRB™) and transcutaneous vagus nerve stimulation (Nemos® tVNS) on patients diagnosed with FM. Consenting FM patients (*N* = 112) who are referred to the Department of Pain Management and Research at Oslo University Hospital, in Oslo, Norway, will be randomized into one of four independent groups. Half of these participants (*N* = 56) will be randomized to either an experimental tVNS group or a sham tVNS group. The other half (*N* = 56) will be randomized to either an experimental MNRB group or a sham MNRB group. Both active and sham treatment interventions will be delivered twice per day at home, 15 min/morning and 15 min/evening, for a total duration of 2 weeks (14 days). Participants are invited to the clinic twice, once for pre- and once for post-intervention data collection. The primary outcome is changes in photoplethysmography-measured heart rate variability. Secondary outcomes include self-reported pain intensity on a numeric rating scale, changes in pain detection threshold, pain tolerance threshold, and pressure pain limit determined by computerized pressure cuff algometry, blood pressure, and health-related quality of life.

**Discussion:**

The described randomized controlled trial aims to compare the efficacy of two vagal nerve innervation interventions, MNRB and tVNS, on heart rate variability and pain intensity in patients suffering from FM. This project tests a new and potentially effective means of treating a major public and global health concern where prevalence is high, disability is severe, and treatment options are limited.

**Trial registration:**

ClinicalTrials.govNCT03180554. Registered on August 06, 2017.

## Background

Chronic widespread pain (CWP), including fibromyalgia (FM), is one of the most difficult chronic pain conditions to successfully treat [1]. CWP is characterized by long-lasting pain that persists for longer than 3 months in multiple regions of the body and is commonly associated with a variety of psychophysiological symptoms such as fatigue, cognitive impairments, and psychological distress [2]. Available CWP/FM treatments provide only modest improvements in pain and minimum improvements in both physical and emotional functioning [3]. Opioids fail to alleviate pain intensity and function [4] and cause a myriad of adverse side-effects [5] while complementary and alternative treatments have only weak to moderate effect sizes for treating CWP [6]. However, vagal nerve innervation may provide us with innovative and successful opportunities to target the complex psychophysiological framework of FM [7–9].

Preliminary intervention trials on humans [10, 11] have shown that vagus nerve stimulation (VNS) can modulate multiple pathophysiological mechanisms inherent in various CWP conditions such as FM: VNS has shown to strongly reduce peripheral inflammatory cytokines [12] decrease sympathetic tone [13], decrease oxidative stress [14], and reverse pain-related brain activity patterns [7, 15]. To date, VNS has been traditionally administered through invasive procedures, known as invasive VNS (iVNS), which typically involves the surgical implantation of electrodes around the vagus nerve [9]. However, iVNS has a high risk for adverse events [16] that often requires removal of the iVNS device. An effective noninvasive alternative to iVNS is transcutaneous VNS (tVNS). The tVNS system sends electrical impulses safely through the skin of the outer ear straight into the auricular branch of the vagus nerve [17]. Another noninvasive approach of vagal stimulation could be through contemplative-based practices and respiratory means.

Various forms of paced slow breathing have also shown to influence brain electrical activity which may be mediated by VNS arising from the diaphragm [18]. This cardiorespiratory stimulation of the vagus nerve may explain some of the overall positive emotional and cognitive benefits of diaphragmatic breathing (DB) [19]. However, the positive analgesic effects deep breathing may have on some acute pain conditions has failed to be established for CP conditions such as CWP [8]. In particular, research on mindfulness-based meditation interventions show contradictory findings [20], differences in conceptualization and practice [21], positive report biases [22], and only small to moderate effect sizes for treating pain in clinical populations [7, 23, 24]. Experimental evidence elucidating the underlying psychophysiological mechanisms of how deep breathing may be used to treat CWP is lacking and often inconsistent [8]. DB as a means of VNS may potentially decrease the pathophysiological processes involved in central sensitization as seen in FM. This action may be the mechanism by which VNS reduces widespread musculoskeletal pain in FM and other comparable pathologies [9].

Due to the strong bidirectional relationship between pain, respiration, and the vagus nerve, a recent systematic review [8] called for future research to identify the autonomic and cardiovascular mediators that link respiration and pain, identify the physiological mechanisms needed to reduce pain, identify the central mechanisms responsible for producing hypoalgesia, and identify the psychological (i.e., behavioral) mechanisms needed to reduce pain. New approaches to testing the efficacy of delivering noninvasive VNS for pain as well as designing new contemplative-based approaches that can potentially optimize vagal tone in order to treat those with CP are needed [7].

## Methods/design

### Aim

The primary aim of this protocol article is to describe the design of a randomized controlled clinical trial investigating the effects of motivational nondirective resonance breathing (MNRB) and transcutaneous vagus nerve stimulation (tVNS) on photoplethysmography (PPG) measured heart rate variability (HRV) in patients diagnosed with FM. Secondary outcomes are changes in self-report numeric rating scale (NRS) pain intensity, pain detection threshold (PDT), pain tolerance threshold (PTT), and pressure pain limit (PPL) determined by computerized cuff-pressure algometry (CPA), blood pressure (BP), and health-related quality of life. The principal objective is to explore the following four research questions:
Does a standardized sham-controlled tVNS intervention or MNRB intervention have effects upon PPG- measured HRV?Is a substantial change in HRV associated with a significant change of self-report NRS pain intensity?Is a substantial change in HRV associated with a change in computerized cuff-pressure algometry PDT, PTT, and/or PPL?Are there changes in BP following either an active or sham tVNS intervention and/or a MNRB intervention?Are there effects on health-related quality of life and behavior following either an active or sham tVNS intervention and/or a MNRB intervention?

### Design

This study will use a single-blind randomized controlled experimental design which will be reported according to the CONSORT statement [25] and the Guidelines for Reporting Articles on Psychiatry and Heart rate variability (GRAPH) [26] in order to expedite translational research efforts and improve research methods, replication, and peer review [27–29] (Table 1). A total of *N* = 112 consenting FM patients will be consecutively recruited and randomized from the Department of Pain Management and Research at Oslo University Hospital, Ullevål, in Oslo, Norway, during the Summer and Fall of 2019. Participants will be randomized to either an experimental tVNS group, a sham tVNS group, an experimental MNRB group, or a sham MNRB group. Both active and sham treatment interventions will be delivered at home, twice a day, for 15 min in the morning and for 15 min in the evening, for a total duration of 2 weeks (14 days). Treatment adherence to both interventions will be monitored electronically through a portable Android device and from a Daily Treatment Journal. An 80% completion of tVNS stimulation and MNRB training (a completion of 23 treatment sessions out of a total 28) will be regarded as adequate adherence in this project. Participants are invited to the clinic twice for pre- and post-intervention data collection. An overview of the participant selection, study design, and study flow is illustrated in Fig. 1.

**Table 1 Tab1:** World Health Organization Trial Registration Data

Data category	Information
Primary registry and trial identifying number	ClinicalTrials.gov NCT03180554
Date of registry in primary registry	08/06/2017
Secondary identifying numbers	Southeast Regional Health Authority, Norway, Project Number: 2017/766 Cristin Project ID: 619480
Source of monetary and material support	Southeast Regional Health Authority, Norway
Primary sponsor	Southeast Regional Health Authority, Norway
Contact for public queries	[name], M.S., M.A., Ph.D. Fellow Email: [contact]
Contact for scientific queries	[name], M.S., M.A., Ph.D. Fellow Email: [contact] Department of Pain Management and Research Oslo University Hospital, Ullevål
Public title	Body versus Machine: Meditative Breathing versus Vagus Nerve Stimulation in the Treatment of Chronic Widespread Pain
Scientific title	Body versus Machine: Motivational Nondirective Resonance Breathing versus Transcutaneous Vagus Nerve Stimulation in the Treatment of Fibromyalgia
Country of recruitment	Norway
Health condition studied	Chronic widespread pain, fibromyalgia
Interventions	Motivational nondirective resonance breathing (active and Sham) Transcutaneous vagus nerve stimulation (active and sham)
Key inclusion and exclusion criteria	Inclusion criteria: • Confirmatory diagnosis of chronic widespread pain, including fibromyalgia; widespread pain index (WPI) ≥ 7 and symptom severity scale (SSS) score ≥ 5 OR WPI of 4–6 and SSS score ≥ 9; generalized pain in at least 4 of 5 body regions must be present; pain symptoms have been generally present for at least 3 months; average pain intensity ≥ 6 on a 0–10 numerical rating scale, where 0 represents “no pain” and 10 represents the “worst pain imaginable” Exclusion criteria: • History and/or presence of comorbid severe neurological or psychiatric disorders (e.g., mania, psychosis, suicidality, bipolar/schizophrenia/autism spectrum disorders); neurodegenerative disorders (e.g., Parkinson’s, Alzheimer’s, Huntington’s disease); pregnancy or planned pregnancy; planned surgery; eating disorder (e.g., obesity, anorexia nervosa); head trauma; migraine; active heart implants (e.g., pacemaker); active ear implants (e.g., cochlear implant); individuals who have practiced meditation consistently (for more than 20 min/day) within the last 6 months
Study type	Randomized controlled clinical trial Interventional Allocation: randomized Intervention model: parallel assignment Masking: double blind (subject, caregiver, investigator, outcomes assessor) Primary purpose: treatment
Date of first enrolment	June 6, 2019
Target sample size	112
Recruitment status	Recruiting
Primary outcome	Heart rate variability (HRV)
Key secondary outcome	Numerical rating scale for average pain intensity; pain detection threshold; pain tolerance threshold; pressure pain limit; blood pressure; credibility/expectancy; health-related quality of life; stress and depression; interoceptive awareness; spirituality; catastrophizing; interference

**Fig. 1 Fig1:**
[figure not shown]
Overview of study design

### Covariates

Sociodemographic characteristics which can have a significant impact upon HRV include age [30], sex [31], body mass index (BMI), waist-to-hip ratio (WHR), physical activity levels [32], usual sleeping habits and hours slept prior to clinical visitation, meal consumption within 2 h prior to clinical visitation, oral contraceptive use for women, habitual levels of alcohol [33], nicotine [34], and caffeine intake. Cardiovascular diseases [35], psychophysiological disorders such as depression and anxiety [36], as well as various cardioactive medications have a considerable impact upon HRV and pain and will be accounted for. In addition, antidepressant classes (e.g., tricyclics) [37], some antipsychotic classes (e.g., clozapine) [38], benzodiazepines [39], antihypertensives [40], some types of statins, and some prescription pain medication use may significantly affect HRV and will be recorded. Non-prescription pain medication as well as sleep aids will also be documented.

### Inclusion criteria

Participants must be between the ages of 18 and 65 with an average NRS of 6–10 [41] and must have a confirmatory diagnosis of chronic widespread pain (CWP), including fibromyalgia (FM), (Read Code: MG30.01) as defined in the ICD-11 [42]. CWP is currently defined by the American College of Rheumatology 2010/2011 criteria to be a fundamental feature of FM, defined as pain lasting ≥ 3 months, located axially, above and below the waist, and on both sides of the body with physical symptoms that include fatigue and waking unrefreshed [43]. This study will use the 2016 revision to the 2010/2011 FM diagnostic criteria [44] which introduces important changes based on experience both within clinical and research settings. A participant included in this study must satisfy the following 3 conditions:

Widespread pain index (WPI) ≥ 7 and symptom severity scale (SSS) score ≥ 5 OR WPI of 4–6 and SSS score ≥ 9.Generalized pain, defined as pain in at least 4 of 5 regions, must be present. Jaw, chest, and abdominal pain are not included in generalized pain definition.Symptoms have been generally present for at least 3 months.A diagnosis of fibromyalgia is valid irrespective of other diagnoses. A diagnosis of fibromyalgia does not exclude the presence of other clinically important illnesses [44].

### Exclusion criteria

Participants must not have any past history and/or presence of comorbid severe neurological or psychiatric disorders (e.g., mania, psychosis, suicidality, bipolar/schizophrenia/autism spectrum disorders) [26] and/or neurodegenerative disorders (e.g., Parkinson’s, Alzheimer’s, Huntington’s disease). Participants will be further excluded on pregnancy or planned pregnancy [45]; planned surgery; receiving treatment for any type of eating disorder (e.g., obesity, anorexia nervosa, etc.) [46]; head trauma; migraine; active heart implants (e.g., pacemaker) [47]; and active ear implants (e.g., cochlear implant). Individuals who have practiced meditation consistently (for more than 20 min/day) within the last 6 months will also be excluded [48].

### Enrolment procedure

Study and contact information will be posted and updated regularly on the Oslo University Hospital website, ClinicalTrials.gov, CRISITN (Current Research Information System In Norway), and various social media platforms. After reading about the study, interested participants are instructed to log in to Nettskjema—a secure digital data management and collection system in Norway—and fill out a brief digital inclusion/exclusion form consisting of exclusion criteria, diagnostic criterion for FM, and an NRS scale. If participants meet self-reported inclusion criteria, they will be contacted by testing administrators with an invitation to participate and an appointment day and time for both clinical visitation I (CVI) and clinical visitation II (CVII) at the Department of Pain Management and Research, Oslo University Hospital.

Upon arrival at the Department for CVI, participants are provided with an informed consent. At this time, participants will have the opportunity to ask any of the testing administrators questions about the study and their contribution. Once the informed consent is signed, participants will be formally enrolled into the study.

### Data management

This study will use Viedoc—an electronic data capture web-based solution used for clinical trial data collection and management that complies with all relevant health regulations [49] and the FDA Code of Federal Regulations 21 Part 11. The Clinical Trial Unit at Oslo University Hospital will perform the setup and design of our Viedoc electronic case report form (eCRF) and audit the study flow throughout the trial period. Testing administrators will actively use Viedoc for all participant data entry throughout the entirety of the study. Signature of the testing administrator is reacquired to ensure the completeness and accuracy of the participant data that has been obtained in the eCRF.

Data omissions and/or corrections in Viedoc will be justified and accounted for within the eCRFs. After the database is locked, the investigator ([name]) will receive a digital copy of the subject data for archiving at the investigation site. The data will be securely stored at the research site database at Oslo University Hospital. Data will be de-identified so that each study participant is only recognizable by his/her unique Viedoc trial subject number. The data will be stored 5 years for further analyses and voluntary follow-up 6 months, 1 year, and 3 years after study closure.

### Randomization and blinding procedure

#### Randomization

The computer-generated randomized allocation sequencer will be imported into the Viedoc eCRF system and made available to testing administrators. Only testing administrators will have access to participant treatment allocation and the allocation will not be available until the participant has signed the informed consent and deemed eligible to participate in the study.

This investigation will use a list randomization recruitment method [50] for CVI where participants will be randomly allocated to receive one of the four treatment groups: tVNS #1 (active); tVNS #2 (sham); MNRB #1 (active); MNRB #2 (sham). The randomization will be stratified by sex (male = 1, female = 2) and cardioactive medications (yes = 1, no = 0) with varying block size within strata. Viedoc will generate the randomization number as well as the allocated treatment group for each participant.

Participants will be considered as taking cardioactive medication if they report that they are currently taking any medication for high BP, cholesterol, heart disease, or prescription pain medication. Participants will also be considered as taking cardioactive medication if they answer that they use tranquilizers, antidepressants, and/or antipsychotics either “less than every week,” “every week, but not daily,” or “daily.” Participants are permitted to continue taking any previously prescribed pain medications/psychopharmacological treatments that are necessary during the trial period.

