Missing data will be treated as follows: If the first (morning pre-intervention) NRS/HRV recording is missing, the last (evening post-intervention) NRS/HRV recording will be used from the night before. If the second (morning post- intervention) NRS/HRV recording is missing, then the first (morning pre-intervention) NRS/HRV recording will be used. If the third (evening pre-intervention) NRS/HRV recording is missing, then the first (morning pre- intervention) NRS/HRV recording will be used. Finally, if the last (evening post-intervention) NRS/HRV recording is missing, then the third (evening pre-intervention) NRS/HRV recording will be used. If all morning and evening NRS/HRV recordings are missing from a day, then NRS/HRV recordings from the day before will be used based upon the assumption that improvement/change is not present. The patient-reported outcome measures will be modeled by repeated measures and fitting random effects models with random slopes. Random effects models are considered the gold standard when analyzing repeated measures and handling missing data in longitudinal design [59, 60].

Baseline characteristics as mean with standard deviation or median with interquartile and frequency with percentage will be described for the four participant groups, active and sham. The change from the first to second data points will be calculated for the 14-day treatment session in regard to HRV and NRS present pain intensity. The change from CVI to CVII HRV, NRS present pain intensity, and NRS average pain intensity will be determined. Difference in changes between the groups in the morning session and evening session will be examined and tested by using two-way analysis of variance (ANOVAs) or random intercept and slope models. For overall difference in the changes between the four groups regardless of morning, evening or days, random intercept models or repeated one-way analysis of variance (ANOVAs) will be used to analyze the data. The tests will be two-sided, and the significance level will be set to 0.05.

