### Data collection procedure

#### Clinical visitations I and II (Fig. 6)

Testing administrators will conduct all data collection for CVI and CVII at the Department of Pain Management and Research under the supervision of the principal investigator. All data will be collected by the same assessor throughout each visitation. From 8:00 to 12:30, three participants will be consecutively registered upon arrival at the Department and directed to the clinical visitation room by an assigned testing administrator. Upon entering the visitation room, each participant will be given an informed consent and will be offered the time to ask any questions in regard to what is required of them for their participation. Upon signing the informed consent, measurements of height, weight, BMI, and WHR will be made. Participants will be instructed to remove any heavy clothing and footwear when on the digital electronic floor scale. BMI will be calculated as weight in kilograms divided by the square of the height in meters (kg/m^2^). After recording the aforementioned measurements, participants will sit in a relaxed semi-Fowler position (30° tilt from the horizontal) with feet flat on the floor, hands on thighs, and palms facing upward for the remainder of the clinical visitation. Any discrepancies to the procedure will be logged in Viedoc and kept for the remainder of the study period and will be included as a potential confounder in analyses.

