In order to acclimatize to the HRV recording environment, each participant is instructed to remain seated for at least 5 min [98] prior to taking the first HRV measurement (Fig. 7a). Acclimatization helps reduce HRV changes due to posture changes [99, 100] and can also reduce confounds subsequent to participant test anxiety [26]. Immediately following the 5 min acclimatization period, three 1-min HRV recordings will be taken on the tip of the right index finger of each participant separated by 1-min intervals. The beginning and end of each of the three HRV recordings will not be announced due to the impact of attentive states and test anxiety on respiratory frequency [101] and HRV recordings [102]. An average of the last two recordings will be used as the baseline measure.

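### The analysis of change names neither the CVI baseline value nor the two stratification factors, which costs precision and leaves the Covariates section unconnected to the models

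*Protocol article*

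**What the plan says.** - **Randomization.** "The randomization will be stratified by sex (male = 1, female = 2) and cardioactive medications (yes = 1, no = 0"). There are four arms, and block sizes vary.
- **Clinical visitations I and II.** Three one-minute HRV recordings are taken after acclimatization. "An average of the last two recordings will be used as the baseline measure".
- **Statistical considerations and sample size calculation, outcome.** "The change from CVI to CVII HRV, NRS present pain intensity, and NRS average pain intensity will be determined".
- **Same section, tests.** "Difference in changes between the groups in the morning session and evening session will be examined and tested by using two-way analysis of variance (ANOVAs"). The stated alternative is a mixed model in which both intercept and slope are random. For the overall four-group comparison, "random intercept models or repeated one-way analysis of variance (ANOVAs) will be used to analyze the data". Patient-reported outcomes are to be modelled as repeated measures by random effects models with random slopes. No model term for baseline, sex or medication is named in any of these sentences.
- **Covariates.** "Sociodemographic characteristics which can have a significant impact upon HRV include age [30], sex [31"], followed by many others. Also, "various cardioactive medications have a considerable impact upon HRV and pain and will be accounted for". The section does not say whether this means a model term, the stratification itself or recording only.
- **Clinical visitations I and II, procedure.** Deviations from the clinic procedure are logged at either visit and "will be included as a potential confounder in analyses".

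**The concern.** Three kinds of variable are handled in separate places that are not joined up.

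1. **Baseline value.** The outcome is fixed as change, and baseline HRV is not named as a covariate anywhere. A change score subtracts the whole baseline value, which is more than the optimal correction whenever the pre-post correlation is below 1. With 28 per arm, that precision is worth having.
2. **Stratification factors.** Stratified blocks balance sex and medication across arms. If these factors predict the outcome analysed, a model without them leaves their variance in the residual and overstates the standard error. The Covariates section points towards using them; the analysis text does not.
3. **Procedure discrepancies.** The one adjustment explicitly promised for the analyses covers both visits. A discrepancy at CVII arises after two weeks of treatment, and adjusting for something that treatment may have affected can bias a randomized comparison.

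At stake are precision, some power, and an analysis that can be read in more than one way.

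**Working it through.** **Inputs.** From the protocol: two-sided alpha 0.05, large effect 0.9, 21 per group for power 0.8, 28 per group for power 0.9, four equal arms (N = 112). Assumed, because the protocol gives neither: the pre-post correlation r, and the share R² of the variance of change explained by the strata.

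**Step 1: the plan's own figures.** A two-sample t-test at d = 0.9 needs 20.4, so 21, per group for power 0.8. With 28 per group its power is 0.911 (0.920 by the normal approximation). Both stated figures are reproduced with no covariate in the model.

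**Step 2: omitting the baseline.** With equal SDs at both visits (set to 1), the variance of a change score is 2(1 − r), and the residual variance after baseline adjustment (ANCOVA) is 1 − r². The variance ratio ANCOVA/change is (1 − r²)/(2(1 − r)) = (1 + r)/2, and the SE ratio change/ANCOVA is √(2/(1 + r)). Power is for 28 per group by the normal approximation, with 0.9 taken on the change-score SD.

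| r | (1 + r)/2 | Change-score SE larger by | Power, change | Power, adjusted |
|---|---|---|---|---|
| 0.3 | 0.65 | 24% | 0.920 | 0.987 |
| 0.5 | 0.75 | 15% | 0.920 | 0.973 |
| 0.7 | 0.85 | 8.5% | 0.920 | 0.955 |
| 0.9 | 0.95 | 2.6% | 0.920 | 0.933 |

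In sample-size terms, 28/0.75 = 37 per arm at r = 0.5 and 28/0.85 = 33 at r = 0.7.

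The gain is more useful away from the planning case. By t-test at r = 0.5:
- 21 completers per arm, d = 0.9: power 0.81 on change and 0.91 adjusted (0.9/√0.75 = 1.04).
- 28 per arm and the protocol's medium effect of 0.5: power 0.45 on change and 0.56 adjusted (0.5/√0.75 = 0.58).

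The protocol does not say which SD the 0.9 refers to. On the SD of a single visit, change-score power with 28 per group would be 0.812 at r = 0.3 and 0.92 or more from r = 0.5 upwards.

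**Step 3: omitting the strata.** Simulation of one active-sham pair within a four-arm trial of 112, with stratified blocks of 4 or 8 and 4000 runs. Assumed: 10% men, 60% on cardioactive medication, and R² split equally between the two factors. Simulation error on a 5% rejection rate is √(0.05 × 0.95/4000) = 0.003.

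| R² | Mean model SE, unadjusted | True SD of estimate | Type I error, unadjusted | Type I error, adjusted |
|---|---|---|---|---|
| 0 | 0.265 | 0.270 | 0.056 | 0.054 |
| 0.05 | 0.266 | 0.260 | 0.041 | 0.043 |
| 0.1 | 0.266 | 0.258 | 0.042 | 0.051 |
| 0.2 | 0.267 | 0.242 | 0.033 | 0.051 |
| 0.3 | 0.266 | 0.230 | 0.023 | 0.050 |

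The unadjusted SE is too large by 0.266/0.258 = 3%, 0.267/0.242 = 10% and 0.266/0.230 = 16% at R² = 0.1, 0.2 and 0.3. At R² = 0 there is no systematic misstatement. Power at d = 0.9 is 0.917, 0.926 and 0.941 unadjusted against 0.930, 0.957 and 0.978 adjusted, for the same three values.

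**Step 4: when the CVI measures are taken.** In the order given under Clinical visitations I and II, the pain ratings come before allocation is generated. HRV, blood pressure and cuff algometry come after allocation but before the assigned treatment is introduced. The questionnaires come last, after a five-minute trial of that treatment. The global impression of change (PGIC) is collected only at CVII. The CVI value is therefore a clean covariate for the first four measures, but not equally for the questionnaires.

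**The case against.** **The analysis text names test and model families and does not give a closed list of terms.** It never calls the tests unadjusted, and the Covariates section covers both stratification factors. A full list may sit in an analysis plan that is not shown. This stands in part: for sex and medication the fault is a missing link between two sections, not a decision to exclude them. It does not cover baseline HRV, which is named as a covariate nowhere although the outcome scale, the tests and alpha are all stated.

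**A reader might infer that the standard errors, and so the p-values, are wrong.** The documents do not support that in general. Omitting the baseline leaves a valid SE and, under randomization, an unbiased comparison. Omitting the strata overstates the SE only if they predict the change. The Covariates section speaks of effects on HRV, and a stable effect on level cancels in a change score. Any resulting error is conservative.

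**A reader might infer that the trial is underpowered through this choice.** The stated power is reproduced without adjustment. A shortfall at d = 0.9 appears only if the effect is scaled to the single-visit SD and r is below 0.5, and the protocol states neither.

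**A reader might infer that adjusting for procedure discrepancies will bias the result.** The sentence concerns departures from clinic procedure, and nothing in the protocol shows that treatment affects these. Bias at CVII is possible but not demonstrated.

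**Conclusion.** The point holds as a matter of precision and coherence. The analysis text fixes change as the outcome, omits the CVI value and both stratification factors, and is not connected to the Covariates section.

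Omitting baseline HRV makes the SE about 3% to 24% larger than necessary for r from 0.9 down to 0.3. Omitting the strata makes the test conservative if they predict change, with type I error of 0.042 to 0.033 at R² of 0.1 to 0.2, and has no systematic effect if they do not. False positives are not inflated, and the stated power at an effect of 0.9, taken on the scale of the variable analysed, is not undercut.

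These sizes rest on assumed r and R², equal SDs at the two visits, and the assumed make-up of the strata. The change is worth making because it is nearly free and helps most if dropout is heavy or the true effect is below 0.9.

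**What to change.** Amend the analysis paragraphs under Statistical considerations and sample size calculation as follows:

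- **HRV, NRS, blood pressure and cuff algometry, CVI to CVII:** the model includes the CVI value of the same measure, taken before the assigned treatment is introduced, plus sex and cardioactive medication (yes/no).
- **Daily mixed models:** the same three terms.
- **Patient-reported questionnaires:** include the two stratification factors. Add the CVI score only where one exists, so not for PGIC, and note that CVI questionnaires follow allocation and a five-minute trial of the treatment.
- **Other covariates:** refer to the Covariates section, and limit those in the main model to variables measured before treatment.
- **CVII procedure discrepancies:** use only in a sensitivity analysis, because adjusting for post-treatment variables could bias the comparison.

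The cost is a few sentences and three model terms, with a short exception for the questionnaires. No new data are needed. The change should be dated before database lock, when the investigators first receive unblinded data.
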